It is therefore of interest to observe the profile of more representative protein *antigens* following sublingual delivery, and to compare this with our and others' experience with nasal, oral and injected delivery of antigens. We have selected the L1 protein of Human Papilloma Virus (HPV) as a representative protein antigen to use as a challenge agent to induce immune responses disseminated within the CMIS, and the systemic immune system, which can then be studied and characterised. Each strain of HPV has a unique L1 protein antigen: strains 16 and 18 are associated with cervical cancer in women, and strains 6 and 11 with anogenital warts in both sexes.

The HPV L1 antigens have been selected from a number of potential immunological challenge agents, as they possess several advantageous characteristics for a human immunological challenge agent:

1. They are antigens from the capsid of a human pathogenic virus that infects the genital tract, and therefore representative of a wide number of viral protein antigens.
2. They are available as a pure preparation, suitable for human use, in the licensed HPV vaccine "Gardasil".
3. Their safety via injection has been demonstrated in numerous clinical trials of HPV vaccines, and the UK Dept of Health is engaged in a mass immunisation campaign employing HPV L1 antigen vaccines in healthy young adult women.
4. The optimum safe and immunogenic human dose of L1 antigens has been determined after injection, which provides a guide to the dose suitable for sublingual application.
5. They spontaneously form "Virus Like Particles" in the "Gardasil" preparation. These larger structures are expected to be more readily taken up by sublingual dendritic cells than small proteins or peptides, and so increase the probability of a detectable immune response to the challenge.
6. They are adsorbed onto alum, which has been used for decades in many licensed vaccines. This will aggregate and is expected to further enhance dendritic cell uptake.
7. They are known to reliably induce both serum and genital tract antibody responses in women after injection, and assays to measure responses in genital tract secretions are described. This ensures we will have a reliable positive response group, which we will recruit first to enable assay development for subsequent application to the sublingual challenge group in which immune responses are expected to be lower and less frequent.
8. The "Gardasil" preparation has the advantage of containing 4 different L1 antigens (from strains 6, 11, 16 and 18). Seroepidemiology of women aged 23 (the median age of subjects generally recruited into our studies) in England shows that around 45% already have immunity to at least one of the 4 antigens, but only 15% have immunity to two or more. This means that in our sample we will expect half the subjects not to be immune to any of the antigens, in whom we can study priming and boosting responses to a neoantigen, which is the most interesting aspect of this study - as previous genital tract infection may bias the subsequent response to the sublingual immune challenge.

However, we will also have around half of the subjects in whom we can simultaneously study responses to recall antigens that they have seen before (thereby increasing our prospects of seeing any response at all to sublingual challenge) and neoantigens. While this hypothesis generating study is not powered to analyse subgroup responses to the 4 antigens in detail, by determining subject's serostatus at entry it will be interesting to see if there is any suggestion that prior genital tract infection modulates the response to

cross-reacting antigens. Prior genital infection is essentially a mucosal immunological prime, which may be boosted by the mucosal (sublingual) or parenteral (intramuscular) boost in different ways. It has recently been shown that around 1% of young women have oral infection with HPV, which might theoretically modulate the immune response. However the low prevalence is unlikely to significantly affect the number of subjects being studied. Any observed differences in immune responses between subjects seropositive or seronegative at entry could be further investigated in larger studies.

## **2.2 Challenge Agents**

*Please provide details of challenge agents(s) to be used in the study (including name, manufacturer, country of manufacture, form)*

The challenge agents will consist of purified, recombinant L1 protein antigens from Human Papilloma Virus serotypes 6, 11, 16 & 18.

A single, 0.5 mL pre-filled syringe of "Gardasil" Human Papillomavirus Vaccine [Types 6, 11, 16, 18] (Recombinant, adsorbed) will be used for each challenge, containing:

Human Papillomavirus Type 6 L1 protein 20 micrograms

Human Papillomavirus Type 11 L1 protein 40 micrograms

Human Papillomavirus Type 16 L1 protein 40 micrograms

Human Papillomavirus Type 18 L1 protein 20 micrograms

L1 proteins are in the form of virus-like particles produced in yeast cells (*Saccharomyces cerevisiae* CANADE 3C-5 (Strain 1895)) by recombinant DNA technology, adsorbed on amorphous aluminium hydroxyphosphate sulphate adjuvant (225 micrograms Al), together with the following excipients: Sodium chloride, L-histidine, polysorbate 80, Sodium borate, Water for injections.

Each dose is presented as a suspension in a pre-filled syringe.

The Marketing Authorisation Holder is Sanofi Pasteur MSD SNC, [name]. Vaccines will be purchased through an approved supplier in the UK.

Syringes will be stored in the Pharmacy Area of the Vaccine Institute in a refrigerator (2°C - 8°C).

Vaccine Institute SOPs for receipt, storage, accountability and reconciliation will be followed.

## **2.3 Objectives and Purpose**

*Please Insert a detailed description of the objectives and the purpose of the study*

The purpose of this hypothesis-generating study is to explore in healthy humans the profile of the mucosa-associated and systemic immune systems' response to pathogen-derived protein antigens.

We will induce an immune response in healthy volunteers by the application of immunological challenge agents to the mucosal immune system (locally or via the sublingual lymph nodes), and the systemic immune system (probably via axillary lymph nodes). This immune response will then be characterised by a number of immune assays, and any differences and similarities in the pattern of responses induced by the two systems explored.

We will apply techniques that we have developed and published in previous studies of oral,

nasal and intramuscular challenge, as well as developing new techniques to characterise T cell responses and regulatory, memory and genital tract-associated surface markers.

Initially we will recruit and challenge subjects via the intramuscular route, as this is known to reliably induce systemic and vaginal secretion antibody responses. This will enable us to develop exploratory cellular assays. Once we are confident that the novel assays are performing with acceptable accuracy and reliability, we will recruit subjects to receive sublingual challenge, as this route of challenge is expected to give lower level and less frequent responses due to reduced antigen access across the sublingual mucosa.

Blood will be taken at several time-points for serum antigen-specific antibody levels and enumeration and characterisation of antigen-specific T and B cells using well-established techniques. We will collect cervical and vaginal secretions using well-established techniques within the Vaccine Institute in which secretions are collected onto clinical ophthalmic sponges by gentle application against the wall of the vagina and cervix under direct speculum examination. Secretions are extracted by centrifugation into a preservative buffer that prevents protease degradation, prior to analysis for antigen-specific antibody in ELISA or Luminex assay and neutralisation assay.

**As this is a hypothesis generating study it is not expected that we will be able to characterise all the parameters, in all the assays, in all the subjects.** The core assays will consist of measurement of antigen-specific antibody in serum and cervico-vaginal secretions as these techniques are well established in the literature. The other assays will be exploratory and methodological development.

Specifically we will characterise:

1. Concentration, neutralising activity and isotype profile of antigen-specific antibody in serum and cervico-vaginal secretions

Using published ELISA and Luminex assays with L1 proteins as coating antigens, and virus neutralisation assay, we will measure the levels of IgG and IgA L1-specific antibody in serum and mucosal secretions. A 'mucosal' response will be characterised by IgA>IgG, and a systemic/nasal response by the reverse.

2. Frequency and isotype profile of antigen-specific antibody secreting cells in blood

We will adapt published ELISpot assays (to detect single cells secreting antigen specific antibody *in vitro*) we have developed to detect responses to nasal or oral administration of antigen, to employ L1 proteins as coating antigens. By enumerating IgG and IgA L1-specific antibody secreting cells trafficking in the blood a 'mucosal' response will be characterised by IgA>IgG, and a systemic/nasal response by the reverse. Expression of mucosa-associated homing markers on antigen-specific B cells in blood can be measured by bead extraction, but this is not planned in this study.

3. Frequency and profile of regulatory, memory and mucosa-associated homing marker expression on antigen-specific T cells in blood measured by CFSE proliferation assay

We will update our published T cell assays to detect antigen specific T cells trafficking in the blood following challenge responding *in vitro* to antigen stimulation, using the flow cytometry based CFSE proliferation assay running on a Guava flow cytometer. In addition to enumerating numbers of T cells we will characterise intracellular cytokine expression and cell surface markers of responding cells including  $\beta 7$  integrin, CCR10, L-selectin and other markers associated with mucosal or systemic homing, and markers of memory (CD45RO/RA) and regulatory function (Foxp3).

4. Profile of cytokine secretion by peripheral blood mononuclear cells in response to *in vitro*

antigen stimulation measured by ELISA. By measuring secretion of cytokines into the supernatant of cultures of PBMCs stimulated with L1 antigens we will be able to determine mucosal patterns of response (IL17) and the Th1: Th2 bias.

## 2.4 Preclinical and clinical data

*Please insert a summary of findings from non-clinical studies that potentially have clinical significance and from clinical studies relevant to the study (please reference all published findings)*

This study builds on and extends a series of published studies we have undertaken using licensed vaccines as safe human challenge agents to induce an immune response that can then be characterised. Using this approach we have characterised the profile of B and T cell responses following oral and nasal administration and intramuscular injection of model antigens.

Extensive preclinical and clinical data in support of the suitability of the antigens in the Gardasil preparation as challenge agents, and their safety evaluation, are presented in detail in section 5 of the Gardasil SPC (Appendix 3)

Gardasil is an adjuvanted non-infectious recombinant quadrivalent vaccine prepared from the highly purified virus-like particles (VLPs) of the major capsid L1 protein of HPV types 6, 11, 16 and 18. The VLPs contain no viral DNA, they cannot infect cells, reproduce or cause disease. HPV only infects humans, but animal studies with analogous papillomaviruses suggest that the efficacy of LI VLP vaccines is mediated by the development of a humoral immune response.

In clinical studies, 99.9%, 99.8%, 99.8%, and 99.6% of individuals who received Gardasil became anti-HPV 6, anti-HPV 11, anti-HPV 16, and anti-HPV 18-seropositive, respectively, by 1 month Postdose 3 across all age groups tested. Gardasil induced high anti-HPV Geometric Mean Titres (GMTs) 1 month Postdose 3 in all age groups tested.

The efficacy for HPV 16/18 related CIN 2/3 or AIS is based on data from protocols 005 (16-related endpoints only), 007, 013, and 015. The efficacy for all other endpoints is based on protocols 007, 013, and 015. Results of individual studies support the results from the combined analysis. Gardasil was efficacious against HPV disease caused by each of the four vaccine HPV type.

## 2.5 Population

*Please insert a description of the population to be studied (including sample size, participant group, patient group (if applicable)). Please indicate if a vulnerable population is to be studied*

- We will recruit a total of 18 healthy female volunteers, aged 18-35.
- All subjects will be healthy, and will provide written informed consent.
- No vulnerable groups will be included.
- From previous experience we expect the median age to be around 23 years old.
- We expect around half the subjects to be naive for the challenge agents, while the remainder will have had some exposure to one or more of the antigens.

As group size is small in this hypothesis generating study we have elected to recruit a narrow age range, to avoid possible bias due to age-related (hormonal) changes in immune response, especially in the genital tract.

### Group 1:

Protocol 04-02c

We will initially recruit SIX subjects into a positive response group that will receive INTRAMUSCULAR challenge. This will enable us to generate positive reference samples and develop the novel assays, as it is known that intramuscular immunisation with L1 antigens induces systemic and mucosal immune responses.

#### **Group 2:**

Once the novel assays are performing satisfactorily, we will recruit a further TWELVE subjects into the group to receive SUBLINGUAL challenge. It may not be necessary for subjects in group 1 to have completed the protocol before group 2 is recruited.

### **2.6 Dose Rationale**

*Please insert a description of, and justification for the, route of administration, dosage, dosage regimen and treatment period(s)*

A single 0.5 mL vial of "Gardasil" vaccine has been shown through extensive clinical trials to be the optimum safe and immunogenic dose for intramuscular immunisation, and is licensed for use in healthy adult women the UK.

To enable this scientific study to complete within the time and resources available, a shortened 0, 1, 4 month challenge regimen will be employed, which is based on the recommendation of the Gardasil SPC section 4.2: *"If an alternate vaccination schedule is necessary, the second dose should be administered at least one month after the first dose and the third dose should be administered at least 3 months after the second dose"*.

Although sublingual application of antigen is likely to be less efficient at stimulating immune responses due to the physical barrier to passive antigen entry across the sublingual mucosa, the extensive human safety profile of this dose level and dose regimen when injected makes it an appropriate choice for this initial hypothesis generating study.

The tiny (microgram) amounts of L1 protein and alum present no credible risk if swallowed, when compared with the huge (gram) amounts of protein (and other particulates such as toothpaste) swallowed daily. Any swallowed L1 or alum is expected to be immediately degraded by gastric acid and digestive enzymes.

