##### **2.7.2.1 Intramuscular injection**

Section 5.1 of the Gardasil SPC (Appendix 3) details the level of benefit associated with intramuscular immunisation.

In clinical studies, 99.9%, 99.8%, 99.8%, and 99.6% of individuals who received Gardasil became anti-HPV 6, anti-HPV 11, anti-HPV 16, and anti-HPV 18-seropositive, respectively,

by 1 month Post-dose 3 across all age groups tested. Gardasil induced high anti-HPV Geometric Mean Titres (GMTs) 1 month Post-dose 3 in all age groups tested. This level of immunity was associated with high levels (100%) of protection against cervical cancer lesions. Subjects over 18 are not eligible for the free NHS mass immunisation programme and so will benefit from a free vaccination (currently approximately £120 per injection).

Subjects already infected with HPV can expect to gain no benefit against the serotype with which they are infected, but will be protected against other serotypes. Although we will use an alternative schedule of immunisation, it is one recommended by the Gardasil SPC and subjects can expect to receive a high level of benefit in protection against HPV infection and associated cervical cancer or genital warts.

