### 2.9.2 Acceptable Visit Windows

Visits within the following window periods will not constitute a protocol deviation:

Visits 3, 5 and 8: +/- 1 day

Visits 4, 6, 7 and 9: +/- 2 days

Given the exploratory nature of this study, it will be acceptable to collect and analyze samples taken at the *closest possible time* to the scheduled visit, if the subject is unable to make the scheduled visit. No additional visits are allowed.

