#### **Visits 2, 4 and 7: Antigen delivery and immunology response follow-up**

(Day 0, 28 and 112)

Pulse and temperature recorded. General state of health, concomitant medications elicited to determine any exclusion/withdrawal criteria. Urine pregnancy test carried out.

Blood taken for immunology assays:

- Serum on all visits
- B cell assays visits 2 & 7
- T cell assays on all visits

Vaginal-cervical secretions collected onto a soft ophthalmic sponge using a speculum, for immunology assays.

The HPV antigens are given sublingually (as drops placed onto the undersurface of the tongue) or by injection (into the upper arm muscle) - according to study group.

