### **Dosage regimen**

Three challenges with 0.5 mL of Gardasil will be given either sublingually or intramuscularly on months 0, 1 and 4 (as recommended in the Gardasil SPC).

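### The day 0, 28 and 112 schedule with ±2-day windows does not guarantee the minimum challenge intervals that the protocol quotes from the SPC

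*Protocol*

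**What the plan says.** Section 2.6 (Dose Rationale) describes the regimen as "a shortened 0, 1, 4 month challenge regimen will be employed, which is based on the recommendation of the Gardasil SPC section 4.2". The SPC sentence it reproduces sets two lower limits. The interval between challenges 1 and 2 is to be no shorter than one month. For the later interval, the wording is "the third dose should be administered at least 3 months after the second dose".

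Two later places go further than a regimen based on the SPC. Section 2.17 (Dosage regimen) gives the challenges "on months 0, 1 and 4 (as recommended in the Gardasil SPC". The benefit text in section 2.7.2.1 says of the schedule that "it is one recommended by the Gardasil SPC", and goes on to expect a high level of protection for intramuscular subjects.

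The working schedule is in sections 2.9.1 to 2.9.3. The challenge visits (2, 4 and 7) fall on "Day 0, 28 and 112". The month row of the table in 2.9.1 labels day 28 as month 1, day 56 as month 2, day 112 as month 4 and day 140 as month 5. Section 2.9.2 gives the window "Visits 4, 6, 7 and 9: +/- 2 days" and says that a visit inside its window is not a protocol deviation.

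**The concern.** The quoted SPC limits are minima, but the windows on the second and third challenge visits are symmetric. A planned interval that sits at or below a minimum, with a window that can shorten it, cannot ensure that the minimum is kept. Because in-window visits are not deviations, a challenge given too early against the quoted limit would leave no trace in the deviation record. By contrast, a challenge postponed for severe febrile illness is recorded as a deviation (section 2.16).

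What is at stake is whether two statements are accurate: that the schedule is the SPC-recommended one, and the benefit expectation that section 2.7.2.1 attaches to it. No statistical result is at stake.

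**Working it through.** **Inputs.** Challenge days 0, 28 and 112 (2.9.1, 2.9.3). Window ±2 days at visits 4 and 7 (2.9.2). Quoted minima of 1 month and 3 months (2.6). The protocol does not say what length of month the quoted limits use, so both readings are worked through.

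**Planned intervals.**
- Challenge 1 to 2: 28 − 0 = 28 days.
- Challenge 2 to 3: 112 − 28 = 84 days.

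**In-window intervals.**
- Challenge 1 to 2: 28 − 2 = 26 to 28 + 2 = 30 days.
- Challenge 2 to 3, windows counted from day 0: (112 − 2) − (28 + 2) = 80 to (112 + 2) − (28 − 2) = 88 days.
- Challenge 2 to 3, windows counted from the previous challenge: 84 − 2 = 82 to 84 + 2 = 86 days.

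Section 2.9.2 does not name the anchor. Section 2.16 re-bases later visits on the actual challenge date, but only after a postponement for illness.

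**Reading A: a month is 28 days.** This matches the month row in 2.9.1 (28/1, 56/2, 112/4 and 140/5 all equal 28).
- Minima: 1 × 28 = 28 days and 3 × 28 = 84 days.
- Planned schedule: 28 and 84 days, so both are met exactly with zero slack.
- Window extremes: 26 days is 2 short. 80 days is 4 short, or 82 days is 2 short with the other anchor.
- With windows from day 0 there are 5 × 5 = 25 pairs of in-window days for visits 4 and 7. Visit 4 on day 26 or 27 breaks the first minimum (10 pairs). With visit 4 on day 28, 29 or 30, the second interval is below 84 days in 2, 3 and 4 pairs (9 more). In total 19 of 25 pairs break at least one minimum. The six that do not are (28, 112), (28, 113), (28, 114), (29, 113), (29, 114) and (30, 114).
- With windows from the previous challenge, both minima hold in 3 × 3 = 9 of 25 pairs, so 16 break at least one.

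These are counts of permitted combinations, not predictions of how often subjects would attend on those days.

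**Reading B: calendar months.** Over every start date from October 2009 to September 2010, the planned study period, one month is 28 to 31 days and three months are 89 to 92 days.
- Planned second interval: 89 − 84 = 5 to 92 − 84 = 8 days short.
- Longest in-window second interval: 88 days, still at least 89 − 88 = 1 day short.
- Shortest in-window second interval: 80 days, which is 9 to 12 days short.
- Planned first interval: 28 days reaches one calendar month for 29 of 365 start dates (about 8%). The in-window minimum of 26 days is 2 to 5 days short.

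**Result.** Reading A places the fault in the windows alone. Reading B places it in the planned second interval as well. Neither reading makes the stated conformity secure.

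**The case against.** The strongest reply is that the protocol uses a four-week month throughout. The month row says so, and the durations agree: 20 weeks in the synopsis and a five-month follow-up in section 2.18 are both 140 days. On that convention the planned days satisfy the quoted limits. This stands as far as it goes. A reader might infer from the calendar-month figures that the planned schedule is simply an arithmetic error. The documents do not support that, because the calendar month is only one reading and the SPC itself is not in the text available to check how it counts. The reply does not rescue the windows, which permit shorter intervals under the protocol's own convention.

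Three further inferences are tempting and should not be drawn:

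- *That Group 1 loses its role as the positive reference.* Sections 2.1, 2.5, 2.8 and 2.12 rest that role on the intramuscular route reliably inducing responses. The seropositivity figures of 99.6% to 99.9% are not tied to these minimum intervals, and nothing in the protocol says that a few days would lower the response.
- *That subjects are being misinformed.* Section 2.7.2.1 is protocol risk/benefit text, and the subject information is not available here.
- *That the benefit statement is in doubt for all 18 subjects.* All 18 share the schedule, but the statement concerns the six intramuscular subjects. The twelve sublingual subjects are to expect no benefit (2.7.2.2) and to regard themselves as unimmunised (2.34).

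It is also fair that section 2.6 claims only a basis in the SPC. The unqualified wording is in 2.7.2.1 and 2.17.

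**Conclusion.** The point holds in a limited form. The protocol presents its schedule as SPC-recommended and quotes minimum intervals, but its days and windows together do not guarantee those intervals. With 28-day months the possible shortfall is up to 2 days in the first interval and up to 4 days in the second (2 if windows run from the previous challenge). With calendar months the planned second interval is itself 5 to 8 days short. The conclusion that conformity is not guaranteed depends neither on the length of a month nor on the window anchor; only its size does.

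Severity is low to moderate. The discrepancy is a matter of days. The study is hypothesis-generating with no primary or secondary endpoints (2.11, 2.30), and no analysis depends on the interval. What needs correcting is the consistency between the dosing schedule and the statements made about it.

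**What to change.** Reconcile sections 2.6, 2.7.2.1, 2.9.1, 2.9.2, 2.9.3 and 2.17:

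1. State what a month means wherever the schedule is given in months.
2. State the challenge schedule in days, and whether the windows on visits 4 and 7 run from day 0 or from the previous challenge.
3. Then either make the days and windows consistent with the quoted minima, or qualify the statements that the schedule is the SPC-recommended one, with the benefit text in 2.7.2.1 to match. The subject information should be checked against whichever is chosen.

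The choice in step 3 belongs to the responsible clinicians, and none is proposed here. If the days change, visits 8 and 9 and the stated duration change with them.

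The cost is a short amendment. The first option may lengthen follow-up slightly. The second may make the benefit statement less favourable.
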